| **Other Measures/Procedural Characteristics:** | **Overall Procedure Time**  Defined as the time measured from the insertion of the hemostasis sheath until the removal of the guide catheter.  **PCI Procedure Time -** Defined as the time measured from the insertion of the guide catheter until the removal of the guide catheter.  **Fluoroscopy Time –** total fluoroscopy utilized during the procedure as recorded by an Imaging System.  **Participant Radiation Exposure** – DAP (dose-area-product) and cumulative dose/air kerma as recorded during the procedure.  **Staff Radiation Exposure** – DAP (dose-area-product) and cumulative dose/air kerma as recorded during the procedure.  **Contrast Fluid Volume in mLs**  **Equipment utilization**  **Operator and staff survey of workload**  **Measurement of Lesion and Stented Segment Length**  Compare (1):   - Visual estimate of segment to be stented by clinical operator prior to delivery of PCI device(s). - CorPath GRX System measurement of the segment planned for treatment with stent. |
|  | Compare (2):   - CorPath GRX System measurement of stent length with known length of stented segment |
|  |  |
| **Participant Population:** | Participants aged 18-85 years with evidence of coronary artery disease and with a clinical indication for PCI will be asked to participate in this study. Planned recruitment of 150 participants per study arm over 3 years. |
|  |  |
| **Inclusion Criteria:** | In order to be eligible to participate in this study the individual must meet all of the following criteria:   1. Age ≥18 years- 85 years 2. Participants with coronary artery disease with clinical indication for PCI 3. Participant deemed appropriate for robotic-assisted PCI 4. Provided a signed and dated informed consent form. |
|  |  |
| **Exclusion Criteria:** | An individual who meets any of the following criteria will be excluded from participation in this study:   1. The investigator determines that the participant or the coronary anatomy is not suitable for robotic-assisted PCI. |
|  |  |
| **Investigational Sites:** | Participants will be enrolled from South Western Sydney Local health District and referred to Liverpool Hospital for the PCI procedure. |
|  |  |
|  |  |
| **Principal Investigator:** | [name], D Med Sc, FRACP FACC  Director of Medicine/Interventional Cardiologist  Liverpool Hospital, NSW Australia University of NSW, Sydney |
|  |  |

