### Equipment utilization (stents, wires, balloons, catheters)

### All equipment used in the PCI will be recorded to perform a cost analysis of technology-assisted PCI versus standard PCI performed by a cardiologist.

## **Lesion Assessment**

The lesion will be measured and recorded by the Cardiologist during the PCI. During the standard care PCI the Cardiologist will measure the lesion as per the institutional procedures. For the technology-assisted PCI the lesion length will be measured with the CorPath GRX System as per the Operations Manual.

The physician will attempt to use the same measuring technique for both pre and post lesion measurements (treatment length and stent length).

A comparison on lesion and PCI device length will be performed:

- 1. Length of segment needing intervention: visual estimate vs. CorPath GRX measurement.
  2. Length of stent(s): manufacturer’s labeled stent length(s) vs. CorPath GRX measurement of implanted stent length(s)

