### CorPath Use Technique

The operator should refer to the CorPath GRX System Operator’s Manual for a detailed description of the system and relevant techniques.

To obtain proper data for analysis, the following procedure, with associated data collection milestones, is recommended, but in no case, dictates use of the CorPath GRX System in a manner different from that presented in the Operator’s Manual:

1. Obtain access using conventional percutaneous catheterization techniques.
2. Once arterial access is obtained, insert a standard guide catheter using conventional techniques. The guide catheter and guidewire of the physician’s choosing shall be used.
3. Manually advance and engage the guide catheter in the coronary artery. Perform angiography to assess the target lesion(s). Record target lesion characteristics such as percent diameter stenosis, etc.
4. Introduce and advance coronary guidewire utilizing CorPath GRX System to target lesion.
5. Record visual estimate of lesion segment (prior to pre-dilatation).
6. Introduce and advance the therapeutic coronary device (balloon/stent) using the CorPath GRX System. The delivery of interventional dilatation and stenting devices to the target lesion (pre-dilation, stent, post dilatation) will be done using the CorPath GRX System. Active guide management may be used to fine tune the placement of or reengage the guide catheter in the ostium of the coronary artery.
7. Measure target lesion using the CorPath GRX System as described in Section 3.5.
8. After stent placement, measure stent length using the CorPath GRX System as described in Section 3.5.
9. Retract balloon/stent system using CorPath GRX System.
10. Retract the guidewire using the CorPath GRX System.
11. Perform completion angiography to assess the target lesion final diameter stenosis and the condition of associated vasculature.
12. Record final fluoroscopy time.
13. Record time of guide catheter removal from the coronary vessel (procedure end time).

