# Data Management, Statistical Analysis and Record Keeping

## **Statistical Methods**

This is a double-arm, open-label, randomized controlled trial of the CorPath GRX System designed to evaluate the safety and effectiveness of the clinical and technical performance of the CorPath GRX System in the delivery and manipulation of coronary guidewires and stent/balloon catheters, and remote manipulation of guide catheters for use in PCI in comparison to standard of care. The analysis of data collected as part of the RCT will include, but may not be limited to, the Objectives and Measures outlined in Section 3.0 of this protocol. Continuous variables will be summarized using the number of observations, mean, standard deviation, median, min and max values. Categorical variables will be summarized with the number and percent in each category out of the number observed. Two-sided 95% confidence intervals may be calculated and two-sided p-values < 0.05 will be considered statistically significant.

The outcome of patient radiation exposure will be analysed using variance (ANOVA). As each participant may have multiple lesions, the outcome of clinical success at day 3 will be analysed using a two level multilevel models. Logit link will be used with a binomial distribution and restricted maximum likelihood (REML) will be used for estimation. Predictor variables in the models will include treatment group.

Technical success will analysed with Fisher’s exact test, comparing the proportion of participants with technical success between the two groups. Logistic regression will be used to compare technical success accounting for lesion complexity. For all other secondary outcomes, continuous outcomes will be measured using independent t-test (or non-parametric alternative depending on distributional assumptions), and categorical outcomes analysed by Fisher’s exact test. For outcomes measured repeatedly over time, multilevel models with an appropriate link functions will be used for analysis.

All statistical analyses will be performed using SAS software (version 9.4) or other widely accepted statistical or graphical software.

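### Section 8.1's independent t-test rule for continuous outcomes does not fit the two length comparisons in Section 2.7, which pair two readings of the same lesion or stent within the robotic arm

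*Protocol*

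**What the plan says.** Section 2.7 (Lesion Assessment) sets out two comparisons. The first is "Length of segment needing intervention: visual estimate vs. CorPath GRX measurement". The second is "manufacturer’s labeled stent length(s) vs. CorPath GRX measurement of implanted stent length(s". The Summary lists the same two and describes the robotic reading in the first as "CorPath GRX System measurement of the segment planned for treatment with stent".

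Section 2.7 provides for CorPath measurement only in technology-assisted procedures; in the standard arm the lesion is measured by institutional practice. Section 7.2.5 takes the readings in one robotic procedure: a visual estimate at step 5, the CorPath lesion reading at step 7 ("Measure target lesion using the CorPath GRX System as described in Section 3.5") and the CorPath stent reading at step 8.

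On analysis, Section 8.1 gives named methods for patient radiation exposure, clinical success and technical success. For every remaining secondary outcome it then states that "continuous outcomes will be measured using independent t-test (or non-parametric alternative depending on distributional assumptions". Its one general provision for correlated data is: "For outcomes measured repeatedly over time, multilevel models with an appropriate link functions will be used for analysis". The lesion-level multilevel model in the same section is confined to clinical success.

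**The concern.** Each length comparison sets two measurements of one object side by side. Neither is a contrast between randomised groups, because no CorPath reading is planned in the standard arm. An independent-samples test treats the two columns of readings as if they came from different lesions. The non-parametric alternative does not help: it is triggered by distribution, not by pairing, and for an independent t-test it would naturally be a two-sample rank test. The multilevel provision does not reach these data either, since two methods applied in one procedure are not repeats over time.

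What is at stake is whether the trial can detect that CorPath systematically over- or under-reads length. The error makes the test conservative, which is not harmless here. When the question is measurement accuracy, a non-significant difference is easily taken for agreement. A test of means also cannot show agreement, because large errors in opposite directions cancel.

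**Working it through.** **The plan's own figure.** The protocol states no power or precision for the length comparisons. Its only calculation, in Section 8.1, concerns patient radiation exposure. With 150 per arm, a difference of 0.20 × 1284 = 256.8 mGy and SDs of 180 and 142.83 mGy, the standard error is √((180² + 142.83²)/150) = √352.0 = 18.8 mGy. Then 256.8/18.8 is about 13.7, far above 1.96, so the stated power above 99% reproduces. It has no bearing on this point.

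**Inputs for the length comparisons**
- From the protocol: two-sided 5% significance; 150 participants in the robotic arm.
- Assumed, because the protocol gives no values: one lesion per participant, so n = 150 complete pairs; equal SDs for the two readings; within-pair correlation r from 0.3 to 0.9; a true systematic shift of 0.2 SD for the power columns.

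**Formulas, in units of one reading's SD**
- Standard error used by the independent test: SE_ind = √(2/n) = √(2/150) = 0.115.
- Actual standard error of the mean difference: SE_pair = √(2(1−r)/n).
- Ratio: SE_ind/SE_pair = 1/√(1−r).
- True type I error of the independent test: 2[1 − Φ(1.96 × SE_ind/SE_pair)].
- Power of the independent test: Φ((0.2 − 1.96 × SE_ind)/SE_pair).
- Power of the paired test: Φ(0.2/SE_pair − 1.96).

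| r (assumed) | SE_pair | SE ratio | True type I error, independent test | Power, independent | Power, paired |
|---|---|---|---|---|---|
| 0.3 | 0.097 | 1.20 | 1.9% | 39% | 54% |
| 0.5 | 0.082 | 1.41 | 0.6% | 37% | 69% |
| 0.7 | 0.063 | 1.83 | 0.03% | 34% | 89% |
| 0.8 | 0.052 | 2.24 | about 0 | 31% | 97% |
| 0.9 | 0.037 | 3.16 | about 0 | 24% | >99% |

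Worked line at r = 0.5: SE_pair = √(1/150) = 0.082. The independent test has power Φ((0.2 − 0.226)/0.082) = Φ(−0.32) = 37%. The paired test has Φ(2.45 − 1.96) = Φ(0.49) = 69%. A simulation of 10,000 trials of 150 pairs agreed closely: at r = 0.5, power was 36.6% independent and 67.9% paired, and the independent test's type I error was 0.5%.

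With complete pairs the point estimate is the same under both tests; only its standard error and p-value change. The independent test also loses power as the readings become more closely related, while the paired test gains it.

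**Timing of the CorPath lesion reading.** In Section 7.2.5, step 6 covers delivery of devices for pre-dilatation, stenting and post-dilatation. Step 7 is the CorPath lesion reading. Step 8, the stent reading, is the only one expressly placed after the stent is in. The Summary describes the lesion reading as that of a segment still to be treated. Steps 7 and 8 both refer to Section 3.5 for instructions, but Section 3 ends at 3.4, so the reference does not settle the order.

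**The case against.** **The rule may not reach these measures.** Section 8.1 applies the independent t-test to remaining secondary outcomes. The length comparisons are never called secondary: the Summary files them under other measures and procedural characteristics. Much of Section 8.1 concerns contrasts between arms, so the protocol could be read as silent here, which a statistical analysis plan may properly fill. This has some force, but it does not remove the point. The protocol labels no individual measure secondary, so the missing label cannot exempt these two. Section 8.1 says its analyses include the protocol's objectives and measures, and the catch-all is the only stated rule that could apply to a continuous length.

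**Comparison 1 might be meant between arms**, with visual lengths from the standard arm set against CorPath lengths from the robotic arm. Section 7.2.5 records the visual estimate within the robotic procedure itself, and the stent comparison cannot be read between arms at all.

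**No formal test may be intended.** Section 2.7 says only that a comparison will be made, and Section 8.1 allows descriptive summaries and further analyses. Reporting paired differences is therefore permitted, but nothing in the text directs the analyst to it.

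**The size rests on assumptions.** This stands. The protocol gives no correlation or SD for length. Conversions to manual PCI and participants who do not proceed to PCI would reduce the number of pairs. Several lesions per participant would add clustering, which if ignored tends to make the standard error too small. A reader might also infer a far larger inflation for stents. With an assumed label SD of 6 to 10 mm and reading error SD e of 1 to 2 mm, √((2·SD² + e²)/150) against e/√150 gives ratios from 0.712/0.163 = 4.4 (SD 6, e 2) to 1.158/0.082 = 14.2 (SD 10, e 1). The arithmetic is sound, but no input except the 150 comes from the protocol.

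**Conclusion.** The point holds as a mismatch between the stated rule and the data. Applied as written, Section 8.1 uses an unpaired test on paired readings. For any positive within-pair correlation, which is to be expected for two readings of one object, the standard error is too large and the test is conservative. The illustrative inflation is 1.4 times at r = 0.5 and 3.2 times at r = 0.9, assuming equal SDs and one lesion per participant. Only the direction follows from the design; the multiples depend on the assumed r. No randomised comparison and no powered outcome is affected, so the correction is worth making but does not threaten the trial's main conclusions.

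Two stronger readings are not supported:
- A reader might infer that the flaw undermines the reduction in unnecessary stents mentioned in Section 1.3.2. That sentence reports an external study, and the protocol nowhere says its own length comparison tests it.
- A reader might infer that step 7 contradicts the Summary. The steps are only recommended and yield to the Operator's Manual, and step 8 alone is expressly placed after stenting, so step 7 may be meant to come before it. The wording is ambiguous and needs clarifying; it is not a demonstrated contradiction.

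**What to change.** In Section 8.1, exempt the two Section 2.7 comparisons from the independent-test rule. State that they are analysed in the robotic arm as within-lesion differences (CorPath minus visual estimate) and within-stent differences (CorPath minus labelled length). Report the mean difference with a 95% confidence interval and limits of agreement. Allow for several lesions per participant, for example with a participant random intercept in a model for the differences. The interval corrects the pairing error; the limits of agreement answer the accuracy question that a test of means cannot.

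As a secondary clarification, reconcile step 7 of Section 7.2.5 with the Summary so that it is clear whether the CorPath lesion reading precedes stenting, and correct the reference to Section 3.5.

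The cost is about two sentences in Section 8.1 and one clarified data-collection milestone. The readings are already planned, and the sample size does not change.

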### Major Adverse Cardiac Events (MACE)

MACE will be measured at each visit of the study.

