A total sample of 300 patients (150 in each group) is sufficient to detect a 20% reduction in radiation exposure to the patient during PCI, assuming a mean radiation exposure of 1284 mGy with standard deviation 180 mGy in the control group, and a standard deviation of 142.83 in the intervention group (29) with greater than 99% statistical power, and two sided statistical significance of 5%.

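### Minor, near-free improvement: for binary outcomes measured once, Boschloo's test would give more power than Fisher's exact test at the same guaranteed 5% level

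*Protocol*

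**What the plan says.** All of this is in the protocol's Statistical Methods section (8.1) unless another place is named.

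- **Level:** "two-sided p-values < 0.05 will be considered statistically significant".
- **Technical success:** "Technical success will analysed with Fisher’s exact test, comparing the proportion of participants with technical success between the two groups". A second, adjusted analysis is added: "Logistic regression will be used to compare technical success accounting for lesion complexity".
- **Other secondary outcomes:** the rule is "categorical outcomes analysed by Fisher’s exact test".
- **Outcomes outside the Fisher rule:** "the outcome of clinical success at day 3 will be analysed using a two level multilevel models", and "For outcomes measured repeatedly over time, multilevel models with an appropriate link functions will be used for analysis". The MACE section under Safety Measures says "MACE will be measured at each visit of the study", so MACE plausibly belongs to the repeated-measures rule.
- **Sample size:** "A total sample of 300 patients (150 in each group) is sufficient to detect a 20% reduction in radiation exposure". This is the only power statement. No event rate, effect size or power is given for any outcome tested by Fisher's test.

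**The concern.** Fisher's test takes the total number of events as fixed. The design fixes 150 participants per arm but not the number of events. When events are few, only a handful of tables share a given total, and the test often cannot get near 5% without exceeding it. Its true error rate then falls well below the nominal level and power is lost.

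Boschloo's test uses the Fisher p-value as its statistic but calibrates it over all possible event totals. It therefore keeps the maximum error rate at or below 5% and rejects every table that Fisher's test rejects, plus some more.

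At stake is the power of the technical success comparison, which is part of the primary objective, and of any other single-time binary outcome with few events. The trial was sized on patient radiation exposure, so nothing in the plan shows power to spare for these comparisons.

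**Working it through.** **Inputs from the protocol.** 150 per arm, 1:1 allocation, two-sided significance at p < 0.05.

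**Assumed inputs.** Event rates, because the protocol gives none for these outcomes. A range of 1% to 10% is used for the true error rate, and several pairs of rates for power.

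**The plan's own power figure.** The difference is 0.20 × 1284 = 256.8 mGy. The pooled SD is √((180² + 142.83²)/2) = 162.5 mGy. The standard error is 162.5 × √(2/150) = 18.8, so the standardised difference is 256.8/18.8 = 13.7. Power is practically 100%, which agrees with the stated figure of above 99%. It does not depend on the choice of test for categorical outcomes.

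**Method.** All 151 × 151 = 22,801 possible tables were enumerated. For event counts x and y, the two-sided Fisher p-value is the sum of the hypergeometric probabilities of all tables with the same total x + y that are no more probable than the one observed. The rejection probability at true rates p₁ and p₂ is

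Σ Bin(x; 150, p₁) × Bin(y; 150, p₂) over the tables in the rejection region.

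The true error rate sets p₁ = p₂.

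**Rejection regions.** Fisher's region is p < 0.05. Its largest true error rate over all event rates is 4.3%. Boschloo's region is Fisher p ≤ 0.0616, the largest cut-off that keeps the maximum at or below 5% (it reaches 4.95%). Boschloo's region contains all of Fisher's rejections and 164 further tables.

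**True two-sided error rate.**

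| Common event rate (assumed) | Fisher | Boschloo |
|---|---|---|
| 1% | 0.2% | 0.8% |
| 2% | 1.2% | 2.3% |
| 5% | 2.4% | 3.4% |
| 8% | 3.0% | 3.7% |
| 10% | 3.3% | 3.9% |

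**Power.**

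| Event rates (assumed) | Fisher | Boschloo | Gain in points |
|---|---|---|---|
| 0% v 4% | 56% | 72% | 16 |
| 0% v 5% | 77% | 87% | 11 |
| 0% v 8% | 98% | 99% | 1 |
| 1% v 5% | 40% | 46% | 6 |
| 1% v 10% | 94% | 95% | 2 |
| 2% v 7% | 44% | 51% | 6 |
| 5% v 12% | 52% | 55% | 3 |
| 10% v 20% | 63% | 67% | 4 |

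Gains are taken from unrounded power.

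**A row that can be checked by hand.** With no events in one arm and 5 in the other, Fisher's p = 2 × (150·149·148·147·146)/(300·299·298·297·296) = 2 × 0.0302 = 0.060. This is not significant, while Boschloo's p is 0.048. With 6 events, Fisher's p = 2 × 0.0302 × 145/295 = 0.030. So against zero events Fisher's test needs 6 and Boschloo's needs 5. At a true rate of 4%, P(X ≥ 6) = 56% and P(X ≥ 5) = 72% for X from Bin(150, 0.04), which is the first row of the power table.

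**The case against.** The strongest reply is that Fisher's test is a valid, standard and prespecified choice, that conditioning on the event total is a defensible position, and that no stated figure in the protocol depends on it. All of that stands. The point is therefore an efficiency suggestion and not a correction.

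Three stronger readings are tempting, and the protocol does not support them.

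- **That Fisher's test governs every categorical outcome.** It does not. Clinical success has a two-level logit model, repeatedly measured outcomes have multilevel models, and technical success also has a logistic regression. MACE plausibly falls under the multilevel rule, and in-hospital MACE enters clinical success. For serious adverse events the protocol promises only a summary.
- **That the stated 5% level is not the level used.** A 5% level is an upper bound, and Fisher's test respects it. Boschloo's test is also below 5% when events are rare (0.8% at a 1% rate), so by that standard it would fail too.
- **That the loss of power is large.** The 16-point gain arises at 0% v 4% and has shrunk to 1 point by 0% v 8%. When both arms have events, the gain in the rows above is 2 to 6 points.

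One counter-argument has some force. Technical failure is defined partly by unplanned conversion to manual operation, which cannot occur in the standard arm, so failures there may be very few. That is an inference from the definition. The other components could still occur in that arm, and a failure rate near 8% or more with robotic PCI would leave almost nothing to gain.

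**Conclusion.** The point holds as a minor improvement. For technical success (unadjusted) and the other two-group binary secondary outcomes measured once, Boschloo's test gives at least the power of Fisher's under the same 5% ceiling. The usual gain is about 1 to 7 percentage points, with more only when one arm has almost no events. These sizes rest on 150 analysed participants per arm and on assumed event rates. The error rate of Fisher's test moves closer to 5% as events become more common. The protocol contains no misstatement or contradiction here, and its sample size is untouched.

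**What to change.** In section 8.1, for two-group binary outcomes measured once, including the unadjusted comparison of technical success, replace Fisher's exact test by Boschloo's unconditional exact test. Name this one test and offer no alternative such as Barnard's, because the choice matters: for 0/150 v 5/150 the p-values are 0.048 (Boschloo) and 0.025 (Barnard). Report each comparison with the risk difference and a score-based 95% confidence interval.

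Keep Fisher's exact test for outcomes with more than two categories, which would otherwise have no test. Leave the logistic regression and the multilevel models unchanged. Make the change before any outcome comparison by arm is seen, since a switch made afterwards would not be credible.

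The cost is one wording change, a test that readers know less well, and slightly more computing. Section 8.1 already allows other widely accepted software. No stated power or sample size changes.
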